**Methods/design:**

The study is a nationwide, multicenter, double-blind, randomized, placebo-controlled trial with a duration of 120 weeks. A total of 18 hospitals and 490 eligible Chinese HBeAg-positive CHB patients will be enrolled and randomly allocated into the experimental group and control group in a 1:1 ratio. Patients in the experimental group will be prescribed TCM formulae (Tiaogan-BuXu-Jiedu granules) plus ETV 0.5 mg per day for consolidation therapy for 96 weeks. Patients in the control group will be prescribed TCM granule placebo plus ETV 0.5 mg per day for the same course. After consolidation therapy, all patients will discontinue their trial drugs and be closely monitored over the next 24 weeks. Once clinical recurrence (CR) occurs, ETV treatment will be restarted. The primary outcome is the cumulative rate of CR at the end of this trial.

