## Recruitment

A total of 490 patients will be recruited by nineteen clinical centers in China nationwide listed as follows: Dongzhimen Hospital affiliated to Beijing University of Chinese Medicine, Shenzhen Traditional Chinese Medicine Hospital, Guangdong Hospital of Traditional Chinese Medicine, Liaoning Hospital of Traditional Chinese Medicine, the First Affiliated Hospital of Guangxi University of Chinese Medicine, Shaanxi Hospital of Traditional Chinese Medicine, Mengchao Hepatobiliary Hospital of Fujian Medical University, Beijing Chinese Medicine Hospital, Beijing Ditan Hospital, Chongqing Traditional Chinese Medicine Hospital, Affiliated traditional Chinese medicine hospital of Southwest Medical University, Shanghai Shuguang Hospital, the Sixth People’s Hospital of Shenyang, 302 Military Hospital of China (the Fifth Medical Center of People’s Liberation Army of China), Shandong Hospital of Traditional Chinese Medicine, the Second People’s Hospital of Tianjin, Public Health Clinical Center of Chengdu, the Third People’s Hospital of Shenzhen, and the Second Hospital of Shandong University. We will recruit volunteers from the outpatient department of the hospitals.

The principal investigators (PIs) of subcenters will introduce the protocol as well as the benefits and risks of the study to the participants before enrollment. In the informed consent form, participants will be asked if they agree to allow the use of their data should they choose to withdraw from the trial. Participants will also be asked for permission for the research team to share relevant data with people from the universities taking part in the research or from regulatory authorities, where relevant. This trial does involve collecting biological specimens for storage. There is no anticipated harm from or compensation for trial participation.

The inclusion and exclusion criteria are listed below. The criteria for premature withdrawal from the study include protocol deviation, pregnancy, or investigator discretion.

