## Inclusion criteria

The inclusion criteria are as follows: (1) diagnosed CHB with positive HBeAg, who has experienced HBeAg clearance and/or seroconversion; (2) aged between 18 and 65; (3) TBIL < 3 × ULN; (4) HBsAg < 5000 IU/ml; (5) TCM symptoms are classified as stagnation of the liver and deficiency of Spleen Qi and Damp-Heat in the liver and gallbladder; and (6) voluntarily sign informed consent.

In the informed consent form, we explain the protocol and clearly inform the participants that after 96 weeks of consolidation therapy, they will stop NA treatment and be closely monitored for the next 24 weeks. Although the procedure complies with the AASLD [21], APASL [22], and EASL [23] guidelines for CHB treatment, there could be potential risks (including virological or clinical relapse) during the off-therapy period, and patients may be required to restart antiviral therapy. Patients are free to quit the trial any time before the off-therapy period.

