## Therapeutic regimen

Patients who meet the inclusion criteria will be allocated in a 1:1 ratio to either the experimental group (EG) or the control group (CG). Patients in the EG will receive TGBXJD granules along with ETV. Patients in the CG will receive TCM placebo along with ETV. The treatment duration is 96 weeks. Those who develop clinical relapse during consolidation therapy (in the first 96 weeks) will be switched to TDF (300 mg per day) according to the guidelines [25] and be removed from the study. All patients who meet the following NA withdrawal criteria in the first 96 weeks will stop their ETV treatment and will be closely monitored in the following 24 weeks: (1) serum ALT persistently within the normal range (under 40 IU/L) and (2) serum HBV DNA persistently undetectable (under 30 IU/mL). Once clinical recurrence is confirmed during the off-therapy period, antiviral treatment (entecavir, 0.5 mg per day) will be restarted immediately (Fig. 1).

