## Interviews

From the first day to the observation point of week 96, we will follow up patients every 24 weeks (± 3 days) and dispatch trial drugs on each visit. In addition, we will retrieve the empty boxes and the remaining doses of each patient for verification and recording. At the end of week 96, patients will be informed again about the potential risks of stopping NA therapy, and additional consent to participate in off-therapy observation will be required. From week 96 to week 120, we will set the intervals between interviews to 4 weeks (± 3 days).

Specimens collected during the trial will be stored in the Biobank of Dongzhimen Hospital. The specimens will be used to reconfirm the readings of existing assessments if necessary, as well as for genetic or molecular analysis in current trials and for future use in ancillary studies.

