## Primary outcomes

The primary outcome will be the incidence of recurrence after ETV withdrawal. Clinical recurrence is defined as a serum aminotransferase (ALT) over twofold of the upper limit of normal (ULN) while the HBV DNA > 2000 IU/mL.

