## Statistics analysis

An independent statistical committee will be in charge of the analysis. The statistical analysis team will conduct the intention-to-treat (ITT) analysis for the primary outcome, where all randomized populations will be included in the full analysis set (FAS). Subjects who violated the protocol will be inspected individually. The last observation carried forward method will be used to impute missing data.

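### The abstract and the consent description stop NA treatment at week 96 without condition, while the Therapeutic regimen section stops entecavir only on ALT and HBV DNA criteria

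*Protocol article*

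**What the plan says.** Three places in the protocol article describe the end of entecavir treatment.

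- **Abstract, Methods/design:** "After consolidation therapy, all patients will discontinue their trial drugs and be closely monitored over the next 24 weeks".
- **Inclusion criteria, on the informed consent form:** the investigators "clearly inform the participants that after 96 weeks of consolidation therapy, they will stop NA treatment".
- **Therapeutic regimen:** "All patients who meet the following NA withdrawal criteria in the first 96 weeks will stop their ETV treatment". Two criteria follow: ALT persistently normal (under 40 IU/L) and HBV DNA persistently undetectable (under 30 IU/mL). The section sets treatment at 96 weeks. It also says that patients with clinical relapse during consolidation are switched to tenofovir disoproxil fumarate (TDF) and leave the study.

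Two other provisions bear on the point. Under Interviews, patients hear the risks again at week 96, and "additional consent to participate in off-therapy observation will be required". Under Recruitment, "The criteria for premature withdrawal from the study include protocol deviation, pregnancy, or investigator discretion". The outcome itself depends on stopping: "The primary outcome will be the incidence of recurrence after ETV withdrawal".

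**The concern.** An unconditional stop and a stop that depends on laboratory results cannot both govern. The difference concerns patients who still have detectable virus or raised ALT at the end of consolidation. As worded, the abstract and the consent description would take them off an antiviral, and the regimen section would not.

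Two things are at stake. One is safety: many centres have to make the same decision about who stops. The other is consent: whether virus must first be undetectable is central to the risk that a participant accepts. The rule also fixes who can have the primary event, since recurrence is counted after ETV withdrawal.

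**Working it through.** The plan gives no figure for this point, so the check compares the texts and then asks whether any other rule makes the difference harmless.

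**1. The rules side by side**

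| Place | Who stops at the end of consolidation | Laboratory condition |
|---|---|---|
| Abstract, Methods/design | All patients | None |
| Inclusion criteria (consent description) | Participants generally | None |
| Therapeutic regimen | Those meeting both criteria | ALT persistently < 40 IU/L and HBV DNA persistently < 30 IU/mL |

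**2. Do the entry criteria ensure that everyone qualifies?** No. The inclusion criteria limit TBIL (below 3 × ULN) and HBsAg (below 5000 IU/ml) but set no limit on ALT or HBV DNA. The exclusion criteria name neither.

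**3. Does removal for clinical relapse take out everyone who does not qualify?** No. Under Primary outcomes, clinical recurrence needs ALT above 2 × ULN together with HBV DNA above 2000 IU/mL. Taking ULN = 40 IU/L from the normal range in Therapeutic regimen, the ALT threshold is 2 × 40 = 80 IU/L. A patient can therefore fail a stopping criterion without reaching relapse.

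**4. A constructed example.** Table 1 schedules HBV DNA and liver function at day 1 and weeks 24, 48, 72 and 96, which is 5 readings during consolidation. Suppose HBV DNA is 500 IU/mL and ALT is 35 IU/L at both week 72 and week 96.

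- Stopping criteria: ALT 35 < 40 is met at these readings. HBV DNA 500 ≥ 30 at the last 2 of 5 readings, so it is not persistently undetectable on any window that includes week 96. The patient does not qualify to stop.
- Relapse: 35 ≤ 80 and 500 ≤ 2000, so there is no relapse, no switch to TDF and no removal.
- Abstract and consent description: the patient stops.

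**5. Do the other provisions settle it?** The second consent under Interviews means that nobody enters off-therapy observation automatically, but it adds no laboratory condition. Investigator discretion under Recruitment is permissive. It concerns leaving the study and does not say whether ETV continues.

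**6. Scale.** The documents give no share of patients expected to miss the criteria. Per 1% of the sample: 0.01 × 490 = 4.9, or about 5 patients.

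**The case against.** The strongest reply is that only the Therapeutic regimen section is an operative stopping rule. An abstract condenses, and the sentence about consent is a short summary under another heading. On the ordinary reading, general statements give way to the specific rule, so investigators who follow the regimen section would act safely. This stands, and it keeps the point minor. A reader might infer that viraemic patients will in fact be taken off entecavir; that would need a site to treat from the abstract or the consent summary, and nothing suggests that any would.

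A reader might also infer that participants are being misinformed. The consent form is not shown and may list the criteria. The next sentence of its description refers to guideline compliance, and the Discussion describes the APASL position as conditional. So the form needs changing only if it carries the same unconditional statement. The published description still conflicts with the regimen section, and unlike the abstract it is main text about what participants are clearly told.

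Third, Fig. 1 is cited at the end of the regimen text and is not shown. It or the full protocol may say what happens to patients who neither qualify nor relapse, and the regimen wording already implies that they do not stop. That part can only be conditional. Unseen material cannot, however, remove a conflict between sentences that are shown.

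Finally, the Interviews section contains no error. It does not say that everyone stops, and a visit paragraph need not repeat laboratory criteria.

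**Conclusion.** The conflict is real, and its correction is minor, on grounds of safety and consent. The abstract and the consent description state an unconditional stop at week 96; the regimen section states a conditional one. Neither the entry criteria nor the relapse rule removes the patients for whom the two differ. Liver function and HBV DNA tests every 4 weeks off therapy, and retreatment on recurrence, limit harm after stopping but do not decide who should stop.

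The number affected is unknown, and the figure of about 5 patients per 1% is for scale only. Because the primary outcome depends on stopping, a reader might infer a loss of power or a biased recurrence rate. The documents do not support that: they give no qualifying share, and how patients who never stop are counted among all those randomized may be set in an analysis plan that is not shown.

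The conclusion rests on two readings. ULN is taken as 40 IU/L, from the normal range in the regimen section. The phrase about the first 96 weeks is read with the stated 96-week duration, so that the criteria are judged by the end of week 96 and do not trigger an earlier stop.

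**What to change.** Let the Therapeutic regimen section govern.

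1. Reword the abstract and the consent description under Inclusion criteria: only patients who meet the regimen section's ALT and HBV DNA criteria by the end of week 96 stop ETV and enter off-therapy observation.
2. Check the consent form, and make the same change there if it carries the unconditional statement.
3. Unless Fig. 1 or the full protocol already says so, add to Therapeutic regimen that patients who neither meet the criteria nor have clinical relapse continue antiviral treatment and do not enter the off-therapy phase. Say there who supplies the drug and follow-up after week 96.
4. Leave the Interviews section as it is.

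The cost is a wording amendment through the memorandum and revised protocol described under Protocol amendments. Recruitment has begun, so if the consent form is affected, the ethics committee must be notified and participant information updated; the week-96 re-consent can carry the update. The wording change needs no extra patients and adds no visits or tests to the trial schedule. Continued treatment for non-qualifiers does need a source of supply, which is why item 3 asks for it to be named.

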## Assessments

To ensure safety and reveal the curative effects of trial drugs, patients will be monitored regularly with assessments throughout the trial (Table 1).

**Table 1 Tab1:** Scheduled assessments

Assessment	Consolidation therapy									Off-therapy observation						Treatment after recurrence
	Day 1	12 w	24 w	36 w	48 w	60 w	72 w	84 w	96 w	4 w	8 w	12 w	16 w	20 w	24 w	Recurrence
**Blood, urinary, and stool routine test**	**√**		**√**		**√**		**√**		**√**						**√**	
**Liver functions**	**√**		**√**		**√**		**√**		**√**	**√**	**√**	**√**	**√**	**√**	**√**	**√**
**Renal function**	**√**		**√**		**√**		**√**		**√**						**√**	
**HBV-serum marker**	**√**		**√**		**√**		**√**		**√**			**√**			**√**	**√**
**HBV DNA**	**√**		**√**		**√**		**√**		**√**	**√**	**√**	**√**	**√**	**√**	**√**	**√**
**Liver biopsy**	**√**								**√**							
**ccc DNA**	**√**								**√**							
**HBcrAg**	**√**		**√**		**√**		**√**		**√**			**√**			**√**	
**HBV pregenomic RNA**	**√**		**√**		**√**		**√**		**√**			**√**			**√**	
**LHBs**	**√**		**√**		**√**		**√**		**√**			**√**			**√**	
**AFP**	**√**		**√**		**√**		**√**		**√**						**√**	
**PT**										**√**	**√**	**√**	**√**	**√**	**√**	
**ECG**	**√**		**√**		**√**		**√**		**√**						**√**	
**Abdominal ultrasound scan**	**√**		**√**		**√**		**√**		**√**						**√**	
**Antibodies of hepatitis A, C, D, E**	**√**															
**CLDQ**	**√**	**√**	**√**	**√**	**√**	**√**	**√**	**√**	**√**			**√**			**√**	
**SF-36**	**√**	**√**	**√**	**√**	**√**	**√**	**√**	**√**	**√**			**√**			**√**	
**The symptom score of TCM**	**√**	**√**	**√**	**√**	**√**	**√**	**√**	**√**	**√**			**√**			**√**	

Patients will be followed up every 12 weeks during the consolidation therapy and every 4 weeks in the off-therapy observation (“w” is short for “weeks”)

*Abbreviations*: *HBV* hepatitis B virus, *ccc DNA* covalently closed circular DNA, *HBcrAg* hepatitis B core-related antigen, *LHBs* HBV large surface proteins, *AFP* alpha fetoprotein, *PT* prothrombin time, *ECG* electrocardiogram, *SF-36* the Short Form (36-item) Health Survey, *CLDQ* the Chronic Liver Disease Questionnaire

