## Discussion

HBV infection remains a major global health concern, as the disease itself and its complications, mainly hepatocellular carcinoma and cirrhosis, caused 887,000 deaths in 2015 alone [26]. Currently, therapeutic drugs for CHB are limited to two types of NAs and interferon. Nucleotide drugs can inhibit virus replication for a long time, but they cannot prevent the synthesis of cccDNA [27], so it is still challenging to achieve clinical cure. Functional cure refers to a continuously negative HBV DNA level and negative conversion or seroconversion of HBsAg, but it can only be realized in a few patients. A systematic evaluation of 34 published studies involving 42,588 patients showed that the annual clearance rate of HBsAg in CHB patients was approximately 1% (including treated and untreated populations) and that in HBeAg-negative patients and HBeAg-positive patients, it was 1.33% (95% CI, 0.76–2.05) and 0.40% (95% CI, 0.25–0.59), respectively [28]. Therefore, lifelong medication is required for most patients. However, long-term treatment with nucleotide drugs has problems that cannot be ignored. Although the rates of resistance to ETV and TDF are low, the likelihood that a patient will develop resistance in the future is unclear. In addition, the high economic burden brought by long-term oral drugs is a vital trade-off factor. The withdrawal of NAs can significantly reduce expenditures for medical care and public health. Additionally, the side effects of NAs cannot be neglected [29], such as the renal toxicity and skeletal toxicity of the first-line therapeutic drug TDF. The new drug TAF bypasses this problem, but its cost is high; thus, the drug has not been widely applied in many countries.

In recent years, some scholars have proposed the concept of immune control, in which the host’s immune system still exerts significant and explicit control over HBV after drug withdrawal; thus, HBV DNA remains at an immeasurable level, and no virology or clinical relapse will occur for a long time after drug withdrawal (beyond 6 months). Therefore, long-term virology inhibition after the withdrawal of nucleotide drugs can be regarded as a possible endpoint of therapy. According to the APASL guidelines, HBeAg-positive patients can discontinue drugs under monitoring by strict follow-up visits after the serological conversion of e-antigen and consolidation therapy for 12 months [22].

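### The rule for stopping ETV does not check HBeAg at week 96, so a patient whose HBeAg has returned could stop; the guideline compliance sentence also needs qualifying

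*Protocol article*

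**What the plan says.** Therapeutic regimen sets the rule: "All patients who meet the following NA withdrawal criteria in the first 96 weeks will stop their ETV treatment". The two criteria are "1) serum ALT persistently within the normal range (under 40 IU/L) and (2) serum HBV DNA persistently undetectable (under 30 IU/mL". They are joined by 'and', and neither HBeAg nor anti-HBe is among them.

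HBeAg appears at entry. Inclusion criterion 1 takes a patient with HBeAg-positive CHB "who has experienced HBeAg clearance and/or seroconversion", so clearance alone is enough. Table 1 (Assessments) has a row "HBV-serum marker" ticked at Day 1 and weeks 24, 48, 72 and 96, then at off-therapy weeks 12 and 24 and at recurrence.

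Two passages concern guidelines. The paragraph on consent under Inclusion criteria reads "Although the procedure complies with the AASLD [21], APASL [22], and EASL [23] guidelines for CHB treatment". The Discussion describes the same APASL reference [22] in these words: "HBeAg-positive patients can discontinue drugs under monitoring by strict follow-up visits after the serological conversion of e-antigen and consolidation therapy for 12 months".

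**The concern.** Entry treats HBeAg loss as a precondition, but 96 weeks pass between entry and stopping, and the stop rule does not ask whether the loss has lasted. The serum markers drawn at week 96 have no role in the decision. Because the rule covers all patients who meet it and says that they will stop, a patient who is HBeAg positive again, with normal ALT and undetectable HBV DNA, would be taken off an effective antiviral. Stopping ETV is the main hazard that participants accept in this trial, so the rule should use the relevant information already being collected.

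The second, smaller matter is wording. The article states compliance with APASL without qualification, describes that guideline elsewhere in terms of seroconversion, and requires seroconversion neither at entry nor at stopping.

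**Working it through.** **1. Is HBeAg part of the decision to stop?**

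| Stage | HBeAg condition | Where |
|---|---|---|
| Entry | clearance and/or seroconversion | Inclusion criteria, item 1 |
| Weeks 24, 48, 72, 96 | markers measured, no action attached | Table 1 |
| Stop | none; ALT and HBV DNA only | Therapeutic regimen |
| Off therapy | markers at weeks 12 and 24 and at recurrence | Table 1 |

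The gap is therefore a return of HBeAg during consolidation while both criteria remain satisfied.

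**2. Does the compliance sentence agree with the Discussion?** The Discussion gives two elements. The duration element (12 months) is met by 96 weeks. Seroconversion is not required at any stage. The mismatch is confined to that element.

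**3. How many patients?** The article gives no rate of HBeAg return. After the planned 20% loss (Sample size estimation), 490 × 0.8 = 392 patients, or 196 per arm, could reach the stop. With an assumed 0.5% to 3%: 392 × 0.005 = 2.0 and 392 × 0.03 = 11.8.

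**4. What would a third criterion cost in power?** Inputs: 32% recurrence and a 12-point difference (Sample size estimation), taken as 32% v 20% with the direction assumed, and two-sided 0.05 (Outcome analysis). Normal approximation to the chi-square test:

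power = Φ{[d√n − 1.96√(2p̄(1−p̄))] / √(p₁(1−p₁) + p₂(1−p₂))}

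With n = 196, d = 0.12 and p̄ = 0.26: (1.680 − 1.96 × 0.6203) / 0.6145 = 0.755, so power is 77.5%. This is the baseline with the full 20% loss. It lies below the planned 80% before any HBeAg criterion is added, so that shortfall does not belong to this point.

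| Not stopping (assumed) | Handling | Rates compared | n per arm | Power |
|---|---|---|---|---|
| 0.5% in each arm | left out | 32% v 20% | 195.0 | 77.3% |
| 3% in each arm | left out | 32% v 20% | 190.1 | 76.2% |
| 0.5% in each arm | non-events | 31.84% v 19.90% | 196 | 77.2% |
| 3% in each arm | non-events | 31.04% v 19.40% | 196 | 75.8% |
| 3%, control only | non-events | 31.04% v 20.00% | 196 | 70.9% |
| 3%, experimental only | non-events | 32.00% v 19.40% | 196 | 81.7% |

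Non-event rates are the underlying rate times the share that stops, for example 0.32 × 0.97 = 0.3104, assuming the same underlying risk in those held back. The observed difference is 11.0 points in the control-only case and 12.6 in the experimental-only case.

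**5. Is there a rule for counting patients who do not stop?** None is shown. Statistics analysis puts all randomised patients in the full analysis set. Missing data excludes cases with incomplete off-therapy ALT or HBV DNA, but does not address a patient who never enters the off-therapy period. Therapeutic regimen and Outcome analysis are also silent. The question already arises for patients who fail the ALT or HBV DNA criterion.

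**The case against.** HBeAg is not ignored: every patient has lost it before entry, and persistently undetectable HBV DNA with normal ALT leaves little room for an undetected return. The 0.5% to 3% range is an assumption with no support in the article. That stands, and it is why the point is minor.

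There are also safeguards. Off therapy, ALT and HBV DNA are tested every 4 weeks, serum markers are repeated at weeks 12 and 24, and ETV restarts on clinical recurrence. Before the stop, "At the end of week 96, patients will be informed again about the potential risks of stopping NA therapy" and fresh consent is taken; investigator discretion is a general ground for leaving the study: "The criteria for premature withdrawal from the study include protocol deviation, pregnancy, or investigator discretion". These limit the harm, but none makes HBeAg a condition of stopping. The flowchart and full protocol are not shown and could hold more detail, but the article states the rule as a complete list.

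The strongest objection is to the remedy. A third criterion is a post-randomisation filter on something the treatment may change. The introduction and the Discussion both report greater HBeAg loss with TCM plus NAs, which suggests that more controls could be held back. That stands too. It applies in kind to the ALT and HBV DNA criteria already in place, and the fix must deal with it.

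A reader might infer that the trial breaches the APASL guideline or that patients are misinformed. The article supports neither. The Discussion's summary is permissive: it says who can stop, not that nobody else may. The guideline texts are not at hand. The compliance sentence stands in a paragraph about the consent form, but the form is not shown.

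**Conclusion.** The point holds as a minor gap in the stopping rule. ETV is stopped on ALT and HBV DNA alone, so a patient who is HBeAg positive again but meets both criteria would stop. How many is unknown and probably very small; 2 to 12 of 392 is an illustration on assumed rates, and 392 itself assumes the full 20% loss. The assessment also assumes that the scheduled serum markers include HBeAg.

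A reader might take this as a threat to the treatment comparison. It is not: the present rule is the same in both arms, and leaving HBeAg out does not bias the randomised comparison. The concern is patient safety and a clear rule.

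The compliance sentence is a secondary wording matter: it does not mention that clearance alone is accepted, while the article's own summary of APASL speaks of seroconversion.

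**What to change.** - **Stop rule (Therapeutic regimen).** Add a third criterion: *(3) HBeAg negative at week 96*, from the serum markers already scheduled, with ETV continued until the result is available. Patients with clearance but no seroconversion can still stop.
- **Counting.** Keep all randomised patients in the full analysis set. State one rule, fixed before unblinding, for how every patient who does not stop ETV enters the primary comparison, whichever criterion failed. Report those patients by arm and by reason, so that any imbalance is visible.
- **Compliance sentence (Inclusion criteria).** Add that HBeAg clearance without seroconversion is accepted, whereas APASL, as the Discussion describes it, refers to seroconversion followed by 12 months of consolidation. Make the same change in the consent form if it repeats the statement.

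Cost: one criterion, one counting rule and one sentence, with no new test or visit; the chi-square test stays. The downside is a small loss of power on the assumed rates: from 77.5% to about 76% if 3% in each arm do not stop, and to about 71% in the least favourable case examined, 3% of controls only counted as non-events.
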